### Statistical analysis

#### Sample size calculation

This is a descriptive, observational study without requirement to power the sample for statistical inference. However, the statistical power for measurement accuracy (i.e. changes of the physical health scale measured by SF-12 from baseline) has been carried out for sample size estimation. This was based on observed variation of the physical health scale in the SF-12 questionnaire in a previous study on a similar population (OVERTURE Study, NCT01430494) [19]. The primary endpoint of the ACQUIRE study is the percentage change between baseline and throughout the observational points in the PCS of the SF-12 questionnaire. Assuming a loss of follow-up of 40% (similar to the 37% rate in the first 18 months of the OVERTURE study), a sample size of 162 patients per CKD stage (486 patients total) allows the detection of an average change of 1.4 points in PCS from baseline to the end of the study with 95% confidence interval (assuming a similar standard deviation [SD] to the OVERTURE study [SD = 7.0]). A 2.5 point change is considered clinically relevant and important in this disease area, so this sample size is sensitive enough to detect clinically relevant changes (1.4 point and above) in patients’ HRQoL [29]. Therefore, the target sample size has been defined as 480 patients. It is expected that approximately 20–25 centers, with 15–30 patients per center will provide the representative sample required in the study.

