#### Statistical analysis of data

Data will be summarized using summary statistics. For continuous data the number of observations, numbers of missing data points, the mean, standard deviation, minimum, first quartile, median, third quartile and maximum will be reported. Counts and percentages will be presented for categorical data. Real-world treatment patterns for ADPKD patients, both overall and CKD stage, will be reported in this way.

The primary efficacy analysis is the change in PCS on the SF-12 questionnaire. For each visit the PCS will be summarized. The absolute values, change from baseline values and mean percentage change from baseline will be reported overall and for each CKD stage. The percentage change will be calculated as follows:
$$ Percentage\ change=\frac{100\times \left( score\  at\  end\  of\ study- score\  at\  baseline\right)}{score\  at\  baseline} $$

The secondary efficacy analysis is the change in the MCS on the SF-12 questionnaire. For each visit, overall and for each CKD stage the MCS will be summarized by the absolute values, change from baseline values and mean percentage change from baseline. The percentage change will be calculated as described above.

The absolute values, change from baseline values and mean percentage change from baseline will be reported for each CKD stage and overall for each questionnaire, at each timepoint. As an exploratory outcome, SEM analysis may be used to identify relationships between variables that could predict PRO scores and other outcomes, such as persistence, the act of continuing treatment for the prescribed duration [30]. Any hypotheses will be developed prior to the analysis of the final data set, but will be based on patient characteristics as baseline. Until baseline results are available, factors that may differ between patient subgroups and any resulting SEM hypotheses cannot be fully defined.

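### The 1.4-point PCS change that the plan calls detectable is a 95% confidence-interval half-width; per-stage power at 1.4 points is about 50%

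*Protocol article*

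**What the plan says.** All of this is in the Protocol article, Statistical analysis, Sample size calculation.

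- The section first says that the study is descriptive and need not be powered for inference. It then says that "the statistical power for measurement accuracy (i.e. changes of the physical health scale measured by SF-12 from baseline) has been carried out".
- The size is "a sample size of 162 patients per CKD stage (486 patients total"), and the loss is set by "Assuming a loss of follow-up of 40% (similar to the 37% rate in the first 18 months of the OVERTURE study").
- The variability is fixed by "assuming a similar standard deviation [SD] to the OVERTURE study [SD = 7.0"].
- The conclusion is that this size "allows the detection of an average change of 1.4 points in PCS from baseline to the end of the study with 95% confidence interval".
- The next sentence names 2.5 points as the clinically relevant change. It concludes that the sample can detect clinically relevant changes, and in parentheses it starts that range at 1.4 points.

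No power level is given anywhere in the section.

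**The concern.** The precision of an estimate and the change a study can detect are different design properties. If the true mean change equals the half-width of the 95% interval, the estimate falls above or below that value about equally often, so the interval excludes zero only about half the time. Nobody would normally call that change detectable.

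The claim concerns the PCS, the primary endpoint, and it is made per CKD stage, a level at which the article says results will be reported. A reader who sees no clear change in one stage could conclude that a mean change of 1.4 points or more has been ruled out, although the study would miss a true 1.4-point change about as often as it found it. The parenthesis adds a second problem: it places 1.4 points inside the clinically relevant range just after relevance has been set at 2.5.

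**Working it through.** **Inputs** (all from Sample size calculation): 95% confidence, taken as two-sided (z = 1.96; the sidedness is not stated); SD 7.0; 1.4 points; 40% loss; 162 enrolled per stage, 486 in total.

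**1. Reproduce the plan's figure as a precision calculation.**
- n = (1.96 × SD / half-width)² = (1.96 × 7.0 / 1.4)² = 9.8² = 96.04, rounded up to 97 completers.
- 97 / 0.6 = 161.7, rounded up to 162 enrolled per stage; 3 × 162 = 486. This matches exactly.
- Back-check: 1.96 × 7.0 / √97 = 1.39 (1.41 with the t quantile), which is the stated 1.4.

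**2. Try it as a power calculation for 1.4 points.**
- Two-sided 5%, 80% power: ((1.96 + 0.842) × 7.0 / 1.4)² = 196.2, so 197 completers and 329 enrolled per stage.
- Two-sided 5%, 90% power: 262.7, so 263 completers and 439 enrolled.
- One-sided 5%, 80% power: 154.6, so 155 completers and about 258 enrolled.

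None of these gives 162. The plan's calculation contains no power term.

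**3. Power per stage with 97 completers.** The standard error is 7.0 / √97 = 0.711, and power = Φ(change / 0.711 − 1.96); the opposite tail is negligible.

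| True mean change | Calculation | Power (normal) | Power (t) |
|---|---|---|---|
| 1.4 | Φ(1.97 − 1.96) | 50.4% | 49.6% |
| 2.0 | Φ(2.81 − 1.96) | 80.3% | 79.6% |
| 2.5 | Φ(3.52 − 1.96) | 94.0% | 93.6% |

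Smallest detectable change:
- 80% power: (1.96 + 0.842) × 0.711 = 1.99 points.
- 90% power: (1.96 + 1.282) × 0.711 = 2.30 points.

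**4. Overall sample.** 3 × 97 = 291 completers. Power for 1.4 points is Φ(1.4 × √291 / 7.0 − 1.96) = Φ(3.41 − 1.96), about 93%.

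**5. Sensitivity.**
- Loss of 37% instead of 40%: 162 × 0.63 = 102 completers, and power for 1.4 points is 52%.
- No loss at all (162 completers): 72%.
- The article does not say whether 7.0 is the SD of the change or of a single score. If it is a score SD, the SD of the change is 7.0 × √(2(1 − ρ)), where ρ is the within-patient correlation. The document gives no ρ, so the values below are assumptions:

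| Assumed ρ | SD of change | 95% half-width | Power for 1.4, per stage |
|---|---|---|---|
| 0.5 | 7.0 | 1.39 | 50% |
| 0.6 | 6.26 | 1.25 | 60% |
| 0.7 | 5.42 | 1.08 | 72% |
| 0.8 | 4.43 | 0.88 | 88% |

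A correlation below 0.5 would give less than 50%. The 162, however, is obtained only by entering 7.0 directly as the SD of the change.

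**The case against.** The strongest defence is that the section signals precision. It disclaims any need for inferential power, speaks of measurement accuracy, attaches a 95% confidence interval to the 1.4 points and states no power. The Study limitations section adds that the PRO analyses are exploratory, without formal hypotheses, and will not support firm conclusions. No test of the PCS change is described, so there is no formal null result to misread. The arithmetic is right, and the size is ample for the plan's own 2.5-point threshold.

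Most of this stands, and it limits the weight of the point. It does not rescue the wording. After disclaiming power, the section makes an explicit claim of detection, twice, at a value where per-stage power is about one half. For a purely descriptive study the matching statement is one of precision.

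A reader might go further and infer that the study is too small, or that the calculation is wrong. The documents support neither: 162 follows exactly from the stated inputs, and per-stage power for 2.5 points is about 94%.

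A reader might also object that the list of summaries, "the mean, standard deviation, minimum, first quartile, median, third quartile and maximum will be reported", contains no confidence interval. That is output detail which an unseen SAP may supply, and the interval can be computed from the reported n, mean and SD. The later sentence that "the target sample size has been defined as 480 patients", against 486 just before it, has no bearing here: 480 × 0.6 / 3 = 96 completers per stage, and the half-width is still 1.40.

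**Conclusion.** The point holds as an error in how a design property is described. The sample size itself is not in error. With 97 completers per stage and 7.0 as the SD of the change, 1.4 points is the half-width of the 95% interval. Two-sided 5% power per stage is about 50% at 1.4 points, 80% at 2.0, 90% at 2.3 and 94% at 2.5. The claim to detect changes of 1.4 points and above therefore fails per stage for changes between 1.4 and about 2.0 points, taking 80% power as the usual standard. It is acceptable for the overall sample, where power at 1.4 is about 93%.

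The 50% figure depends on 7.0 being the SD of the change; under the assumed correlations of 0.5 to 0.8 for a score SD, it would be 50% to 88%. Because the analyses are descriptive and adequacy for 2.5 points is unaffected, this is a minor to moderate correction.

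**What to change.** In Sample size calculation, replace the detection sentence with wording such as:

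> About 97 evaluable patients per CKD stage give a 95% confidence interval of about ±1.4 points around the mean PCS change (SD of change 7.0). The smallest change detectable with 80% power is about 2.0 points, and power for a 2.5-point change is about 94%.

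In the following sentence, delete the parenthesis that starts the detectable and clinically relevant range at 1.4 points, and leave 2.5 as the only relevance threshold. State explicitly that 7.0 is the SD of the change; if it is not, recompute these figures.

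The cost is wording only: no extra patients and no change to design, endpoint or analysis. The downside is a less favourable headline figure per stage, 2.0 points instead of 1.4.

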#### Statistical analysis of data

Data will be summarized using summary statistics. For continuous data the number of observations, numbers of missing data points, the mean, standard deviation, minimum, first quartile, median, third quartile and maximum will be reported. Counts and percentages will be presented for categorical data. Real-world treatment patterns for ADPKD patients, both overall and CKD stage, will be reported in this way.

The primary efficacy analysis is the change in PCS on the SF-12 questionnaire. For each visit the PCS will be summarized. The absolute values, change from baseline values and mean percentage change from baseline will be reported overall and for each CKD stage. The percentage change will be calculated as follows:
$$ Percentage\ change=\frac{100\times \left( score\  at\  end\  of\ study- score\  at\  baseline\right)}{score\  at\  baseline} $$

The secondary efficacy analysis is the change in the MCS on the SF-12 questionnaire. For each visit, overall and for each CKD stage the MCS will be summarized by the absolute values, change from baseline values and mean percentage change from baseline. The percentage change will be calculated as described above.

The absolute values, change from baseline values and mean percentage change from baseline will be reported for each CKD stage and overall for each questionnaire, at each timepoint. As an exploratory outcome, SEM analysis may be used to identify relationships between variables that could predict PRO scores and other outcomes, such as persistence, the act of continuing treatment for the prescribed duration [30]. Any hypotheses will be developed prior to the analysis of the final data set, but will be based on patient characteristics as baseline. Until baseline results are available, factors that may differ between patient subgroups and any resulting SEM hypotheses cannot be fully defined.

The DCE will be analyzed using mixed effect and multinomial logit models, exploring the impact of each treatment attribute on patient choice [31]. Specifically, two relationships will be studied: [i] the relationship between attributes of treatment and overall treatment preference, as captured in the DCE, and [ii] relationship between stated DCE attribute preferences and persistence to ADPKD treatments. Using results from a multinomial logit model, marginal rates of substitution will be calculated to measure how patients trade-off between certain attributes in their decision making; preference heterogeneity will be investigated by incorporating interactions between individual characteristics (such as gender, age, and disease severity) and relevant levels.

No imputation methods will be used to replace missing data; incomplete or missing data will be left as recorded. However, if a date is required for analysis or to define subgroups, the most conservative approach will be used. For example, if an adverse event has occurred, it will be assumed that the event occurred during the study observation phase except if the onset date is partially completed or other data (e.g. a stop date) indicates differently.

A subgroup analysis of tolvaptan use will be performed, investigating longitudinal changes within subgroups and differences between subgroups. In this analysis patients will be split into ‘patients with tolvaptan treatment ongoing at baseline’ and ‘patients with tolvaptan treatment not ongoing at baseline’. A subgroup of ‘patients starting tolvaptan during follow-up’ may also be included.

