#### DCE study

During the first and last study visits, a DCE questionnaire is administered to determine how highly patients value specific attributes of hypothetical alternative treatment options. A DCE is a health economic methodology used to explore the relative importance of each treatment attribute, helping to inform future treatment decisions [26]. DCE studies are used to quantify patient preferences for specific treatment attributes, and to investigate the role each treatment attribute plays in determining patient’s overall preference for a treatment [27]. Patients are offered a choice of hypothetical alternative treatments that are defined by different and varying attributes. Patients are asked to compare these hypothetical treatments and choose which they prefer. The analysis of patient responses across a number of different discrete treatment choices allows individual attributes to be ranked in order of patient preference.

The DCE used in this study was developed to measure patient-perceived relative importance of different treatment attributes (aquaresis, time to kidney failure, risk of serious and permanent liver damage, additional doctor/clinic visits, tablet number and routine). Patients are asked to assigned each attribute to one of 3 levels ranging from equal to the effects of local standard of care (e.g. ‘no additional urination or increased thirst’) to very different from the effects of local standard of care (e.g. ‘you have to go to the toilet and have to drink three times as much’) (Fig. 2). The orthogonal design (where the occurrence and level of each attribute is unrelated to any other attribute) of the DCE allows the assessment of the role and importance of each attribute in determining treatment preference from patient responses. The outcome is expressed as an odds ratio. Cognitive debriefing interviews and a steering committee of experts were used to validate the DCE study design, and a pilot test of the study was performed in a small number of patients (*n* = 5), which demonstrated that the study was internally and externally consistent [28].

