This is also the first study aiming to measure ADPKD patient treatment preference using a DCE. The DCE in this study has been validated by an expert steering committee and aims to investigate the roles of treatment attributes in patient treatment choices. Mixed effect and multinomial logit models are commonly used to analyze patient DCE responses [39], as these models allow each treatment attribute to be valued independently of others and then listed in order of most to least important when patients are choosing between hypothetical treatment options, as well as allowing assessment of how patients trade-off in their decision making and the existence of any preference heterogeneity. DCEs can explore patient preferences for attributes of healthcare interventions, for example treatment efficacy and side-effects, and act as a predictive treatment tool to aid treatment decisions based on patient response. Previously, this methodology has been used to guide treatment decisions in a range of therapeutic areas, including CKD [40–42]. These studies demonstrated that CKD patients value QoL and treatments that improve the day-to-day experience of living with the disease. For example, one study found patients were willing to forgo 23 months of life expectancy if they could receive home dialysis with fewer travel restrictions [41]. Another study found ESRD patients were willing to accept a 6% increase in medication-related heart attack risk to avoid two blood transfusions per month [42].

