The DCE used in this study will provide information about patient treatment preference, based on possible treatment side effects and outcomes. Specifically, the DCE was designed to compare patient tolerance of aquaresis against long-term treatment outcomes. Aquaresis is a known and expected side effect of tolvaptan treatment, and physicians highlighted this as a concern during the development of the DCE in this study. However, there is little evidence on the impact of tolvaptan-related aquaresis on patient HRQoL [10]. The results of this DCE study will provide information about the importance of aquaresis to patients compared with other long-term benefits of tolvaptan treatment, such as delay to ESRD. Additionally, preference heterogeneity in terms of patient characteristics will provide information to help predict specific patient perception of the benefits of treatments. It may thus be easier for physicians, when discussing treatment options with each patient, to predict whether a patient will value the benefits of a treatment, such as tolvaptan, while coping well with potential side effects. This may allow physicians to highlight those patients that have a diagnosis qualifying them for tolvaptan treatment, but also whose HRQoL will be most improved by tolvaptan treatment.

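### As described, the DCE interaction analysis cannot separate different preferences from different response consistency; judge heterogeneity on trade-off ratios instead

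*Protocol article*

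**What the plan says.** Under Statistical analysis of data, the article names the model classes: "The DCE will be analyzed using mixed effect and multinomial logit models, exploring the impact of each treatment attribute on patient choice". It then plans two things from the multinomial logit. First, "marginal rates of substitution will be calculated to measure how patients trade-off between certain attributes in their decision making". Second, "preference heterogeneity will be investigated by incorporating interactions between individual characteristics (such as gender, age, and disease severity) and relevant levels". It does not say that the marginal rates of substitution will be compared between patient groups, and it does not mention the error scale.

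Under DCE study, the attributes are "aquaresis, time to kidney failure, risk of serious and permanent liver damage, additional doctor/clinic visits, tablet number and routine", each at "one of 3 levels ranging from equal to the effects of local standard of care". The same section adds: "The outcome is expressed as an odds ratio". The WHO Trial Registration Data Set lists an overall DCE odds ratio for the whole sample and per CKD stage.

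The intended use appears in the section The ACQUIRE study addresses unmet needs. The models are said to allow assessment of "the existence of any preference heterogeneity", and "preference heterogeneity in terms of patient characteristics will provide information to help predict specific patient perception of the benefits of treatments". The abstract's discussion likewise ties perceived benefit to the values and trade-offs that patients hold. Study limitations labels all DCE analyses exploratory, without formal hypotheses, and rules out firm conclusions.

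**The concern.** The scientific target is a trade-off, for example how much aquaresis a patient accepts for a given delay to kidney failure. A trade-off is a ratio of two coefficients, and the error scale cancels from it. A characteristic-by-level interaction is a difference of raw coefficients, and the scale does not cancel. A non-zero interaction may therefore mean different preferences, different response consistency, or both. Adding random effects does not by itself separate the two.

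If older or more severely affected patients answered a remote web questionnaire less consistently, the interactions could be read as a difference in what they value. The article hopes physicians will use this result to anticipate which patients will value a treatment, so that misreading would matter even in exploratory work.

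**Working it through.** **The plan's own figure.** The article gives no design figure for the DCE. Its one sample-size figure reproduces: n = (1.96 × 7.0 / 1.4)² = 96.04, rounded up to 97. Allowing for 40% loss, 97 / 0.60 = 161.7, so 162 per CKD stage, and 3 × 162 = 486. With 40% loss about 0.60 × 486 = 292 remain. The simulations below use 486 and 292.

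**Why scale enters.** Let β be the preference weights and s the scale of one group relative to another whose scale is 1. The standard logit estimates β in the reference group and sβ in the other. With identical preferences:

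- interaction for level k = sβₖ − βₖ = (s − 1)βₖ, which is non-zero whenever s ≠ 1 and βₖ ≠ 0;
- marginal rate of substitution = sβⱼ / sβₖ = βⱼ / βₖ, whatever s is.

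**Worked example** (assumed weights −0.8 for the worst aquaresis level and +0.9 for the best time-to-kidney-failure level; s = 0.7):

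- Coefficients in the second group: −0.56 and +0.63.
- Interactions: +0.24 and −0.27.
- Odds ratios: exp(−0.8) = 0.45 against exp(−0.56) = 0.57, and exp(0.9) = 2.46 against exp(0.63) = 1.88.
- Trade-off: −0.8 / 0.9 = −0.89 and −0.56 / 0.63 = −0.89, so no difference.

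**Simulation.** From the article: three levels per attribute, and five attributes if tablet number and routine count as one, giving 5 × (3 − 1) = 10 level effects. Assumed, because the article does not state them: 8 or 12 paired choices per patient, log-odds weights of 0.1 to 1.0 in size, a 50:50 split on the characteristic, the scale ratio, and a 5% level. Preferences were identical in both groups. The statistic is the likelihood ratio for all 10 interactions (10 df). The scale-adjusted version first frees one relative scale parameter (9 df). Two sets of runs were made, with 400 and 300 replicates per setting. Rejection rates for the joint unadjusted test:

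| Patients | Choices | Ratio 0.8 (400 reps) | Ratio 0.8 (300 reps) | Ratio 0.7 (400 reps) | Ratio 0.7 (300 reps) |
|---|---|---|---|---|---|
| 292 | 8 | 17% | 20% | 41% | 42% |
| 292 | 12 | 26% | 24% | 64% | 64% |
| 486 | 8 | 29% | 33% | 69% | 66% |
| 486 | 12 | 40% | not run | 85% | not run |

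At equal scale the joint test rejected in 5-6% (400 replicates) and about 4% (300 replicates) of runs. With the relative scale freed, the rates were 3-8% and 3-7% across the scale ratios simulated. In the 300-replicate set the group-specific trade-off had medians of about −0.88 to −0.91 in both groups, against a true value of −0.89.

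**The case against.** The strongest reply is that the article does not contain the error one might charge it with. It says heterogeneity will be investigated; it gives no null, significance level or rule for declaring that groups differ, and Study limitations disclaims firm conclusions. It names model classes only, and a single error scale is a property of the standard model, not wording in the text. The full protocol or analysis plan, not shown here, could adjust for scale. Marginal rates of substitution are already planned, and an interaction model is a usual route to group-specific ones.

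Most of this stands. A reader might infer that groups who merely answer less consistently will be declared to have different preferences, or that a planned test will reject far above its nominal rate. The document supports neither, because no such test or declaration exists in it. Nor do the simulated rates estimate this study's error rate: the scale ratio drives them and is assumed. The article's remark that patients with low quality of life may be less able to complete questionnaires concerns non-completion, not noisier answers. Simulated rates for at least one significant interaction out of ten should also be set aside, since 35-40% of runs showed one at equal scale, which is multiplicity and a separate matter. Finally, listing an odds ratio per CKD stage is reporting by stage; no comparison between stages is stated.

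What does not fall away is the method the article does state. Characteristic-by-level interactions are the only tool it names for heterogeneity, and it does not say that the scale-free quantity will be compared by group. The exploratory label limits the strength of a conclusion; it does not change what the interactions measure.

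**Conclusion.** The point holds in a limited form. In the standard multinomial logit, the stated interactions mix preference with response consistency, so by themselves they cannot support a statement that groups defined by gender, age or severity trade attributes off differently. The algebra needs no assumption beyond the standard form of the model. Whether it matters in this study depends on scale differing between groups, which the article neither shows nor sizes. If it does differ, the effect could be substantial: 17-40% rejection at a ratio of 0.8 and 41-85% at 0.7 for a joint 5% test, against about 5% at equal scale, under the assumed task numbers, weights and split. Severity is low: a cheap improvement to an exploratory analysis.

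**What to change.** In Statistical analysis of data, state that preference heterogeneity will be judged on a scale-free quantity. Either of two routes is enough:

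- report the marginal rates of substitution already planned separately by group, with delta-method or bootstrap 95% confidence intervals for the between-group difference; or
- add a group-specific relative scale parameter to the logit and assess preference differences given that scale.

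Keep the raw interactions as supportive. If DCE odds ratios are compared between CKD stages, apply the same caution there.

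The cost is a sentence or two of wording, a little more analysis work and somewhat wider intervals. No new data are needed.

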### Study limitations

While this study aims to provide valuable insights into the burden of early-stage ADPKD, there are several limitations that should be considered. While study results will potentially provide an indication about the real-world impact of early-stage ADPKD on patient HRQoL and patient treatment satisfaction and preference, all analyses using PRO data and the DCE are exploratory. As a result, no formal hypotheses are provided for these analyses and no firm conclusions from the analyses can be drawn. PROs will be collected remotely, with participants completing the questionnaires via a web-based data capture system. Although this was considered to be the best method of maximizing the response rate, it is still likely that a significant number of patients will not complete the questionnaires. Additionally, this may lead to selection bias as individuals with low QoL may be less able to complete the questionnaires resulting in artificially inflated scores [43]. It may also not be possible to extend the findings of this study to patients with slower progressing ADPKD. Participants have been selected because there is evidence that they suffer from rapidly progressing ADPKD and it is possible that patients with faster progressing disease may be more willing to accept treatment side effects for a relatively short delay to ESRD given that they are more likely to progress to ESRD. Finally, the attributes of the treatment alternatives presented in the DCE are hypothetical. Therefore, the results of the DCE study will be subject to potential hypothetical bias.

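### The primary SF-12 PCS change is summarised from observed cases only, with 40% loss planned: visit means may be inflated, and the change may be biased in either direction

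*Protocol article*

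**What the plan says.** All references are to the protocol article.

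- **Statistical analysis of data, primary endpoint.** "For each visit the PCS will be summarized": absolute values, change from baseline and mean percentage change, overall and per CKD stage. The percentage-change formula needs both a baseline and an end-of-study score. The summary statistics include the number of missing data points.
- **Statistical analysis of data, missing data.** "No imputation methods will be used to replace missing data; incomplete or missing data will be left as recorded". The only exception concerns dates.
- **Sample size calculation.** The recruitment target is inflated for attrition: "Assuming a loss of follow-up of 40% (similar to the 37% rate in the first 18 months of the OVERTURE study". With an SD of 7.0 borrowed from that earlier study and a target precision of 1.4 PCS points at 95% confidence, the section arrives at 162 recruited per stage, or 486 in all. A change of 2.5 points is called clinically relevant.
- **Study procedures and measurements.** The SF-12 is collected at baseline, Month 1, Month 3 and then every 3 months to Month 18, so up to eight PCS scores per patient.
- **Study limitations.** Many patients are expected not to complete the questionnaires, and this may cause selection bias because "individuals with low QoL may be less able to complete the questionnaires resulting in artificially inflated scores".

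The article describes no repeated-measures model, weighting or missing-data sensitivity analysis for PCS.

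**The concern.** A summary of whoever responded is in general unbiased only if being missing is unrelated to PCS. The protocol doubts this itself when it names low QoL as a possible reason for non-completion and inflated scores as the result. It then fixes an analysis that does nothing about it. A patient who stops at Month 12 contributes nothing to the Month-18 change, although up to six PCS scores (baseline and Months 1, 3, 6, 9 and 12) are on file.

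Two results are at stake. The first is the set of visit-level PCS means, which serve the primary objective of describing HRQoL overall and per CKD stage. The second is the mean change and percentage change, which is the primary endpoint. They react differently to selective loss. A reader who follows the visit means over time may draw a different conclusion from one who reads the within-patient change.

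**Working it through.** **1. The plan's own figure.** Inputs from Sample size calculation: SD 7.0 (taken here as the SD of the change), precision 1.4 points, 95% confidence, 40% loss.

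- Evaluable patients: (1.96 × 7.0 / 1.4)² = 96.04, rounded up to 97.
- Recruited: 97 / (1 − 0.40) = 161.7, rounded up to 162 per stage; 3 × 162 = 486.
- Check: 162 × 0.6 ≈ 97, half-width 1.96 × 7.0 / √97 = 1.39.

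The figure reproduces. The inflation replaces lost precision; it does nothing about selective loss.

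**2. Bias as a function of the gap between completers and non-completers.** With a fraction 0.40 missing, bias in mean change = 0.40 × (mean change in completers − mean change in non-completers). The documents give no such gap, so this is a range:

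| Gap (points) | Bias (points) | Benchmark |
|---|---|---|
| 1 | 0.4 | |
| 2.5 | 1.0 | |
| 3.5 | 1.4 | the planned precision |
| 6.25 | 2.5 | the stated clinically relevant change |

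**3. Selection on the change itself.** Assume a normal latent retention variable with correlation ρ to the PCS change. Bias = ρ × 7.0 × φ(Φ⁻¹(0.4)) / 0.6 = ρ × 7.0 × 0.644. The values of ρ are assumptions. Coverage is that of a nominal 95% interval with SE 7.0/√n.

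| ρ | Bias (points) | Coverage per stage (n = 97) | Coverage overall (n = 292) |
|---|---|---|---|
| 0.1 | +0.45 | 0.90 | 0.80 |
| 0.2 | +0.90 | 0.75 | 0.40 |
| 0.3 | +1.35 | 0.52 | 0.09 |

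The bias reaches 1.4 points at ρ = 0.31.

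**4. Direction depends on what drives the loss.** Two-timepoint simulation with 40% missing and change SD 7.0. Assumed: baseline mean 45, baseline SD 8 to 10, true change −1, selection correlation 0.3 to 0.5.

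| Loss driven by | Bias, final level | Bias, change | Bias, % change |
|---|---|---|---|
| low end-of-study PCS | +1.6 to +3.2 | +0.5 to +1.0 | +1.1 to +2.3 |
| decline itself | +0.7 to +1.1 | +1.35 to +2.25 | +3.1 to +5.2 |
| low baseline PCS | +1.0 to +2.4 | −0.5 to −1.0 | −1.1 to −2.3 |
| nothing related to PCS | 0 | 0 | 0 |

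The final level is inflated in every selective scenario. The change is not: when patients with low baseline PCS leave, regression to the mean makes the completers' change too negative.

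**5. Eight-visit simulation.** Assumed: baseline mean 48, cross-sectional SD 9, change SD 7.0, true change −1.5 (true Month-18 mean 46.5), 40% monotone dropout.

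- *Dropout odds 1.65 per 9 points lower previous PCS.* The observed Month-18 mean is about 48.2, or 1.7 points too high. The same completers started at about 49.9, and their mean change is about −1.66. Over SDs of 8 to 10 and several correlation structures it is about −1.6 to −1.7. A likelihood-based mixed model gives −1.48.
- *Dropout driven by the current, unseen change.* Completers show about −0.5 to −0.6. In the run with completers at −0.53, the mixed model gave −1.07. It removed 1.07 − 0.53 = 0.54 of a bias of 1.5 − 0.53 = 0.97, so a little over half. The share depends on the assumed correlation structure.

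**The case against.** The strongest reply has four parts.

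- **The study is descriptive.** Sample size calculation says it is not powered for inference. Study limitations calls all PRO analyses exploratory, discloses the selection risk and allows no firm conclusions, and missing counts will be reported. This stands as a reason for lower severity. It does not remove the point: a description can be biased too, and the study was sized on the accuracy of the PCS change.
- **The protocol says only that bias may occur.** Its remark on low QoL concerns questionnaire non-completion, whereas the 40% is loss to follow-up. This stands. A reader might join the two and infer that the 40% lost will be the low-QoL patients. The document does not say so; all that follows is that both routes leave PCS missing.
- **The primary endpoint is a within-patient change.** A reader might infer that observed-case analysis must bias it upward and make a real decline vanish, since an observed Month-18 mean of 48.2 sits above a true starting mean of 48. This stands against that inference: those completers began at about 49.9 and still show a decline, slightly overstated.
- **Avoiding imputation is not an error, and model details belong in the SAP or full protocol, which are not shown.** The first half stands: a likelihood-based mixed model needs no imputation. The second stands for covariates and covariance structure. But the article does not merely stay silent. It states both the summary method and the missing-data rule.

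**Conclusion.** The point holds as a should-fix. The stated analysis of the primary endpoint uses observed cases only, although the protocol expects heavy loss and names a mechanism by which loss could depend on HRQoL.

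If low-QoL patients are the ones missing, visit-level PCS means are inflated, by about 0.7 to 3.2 points at Month 18 in the two-timepoint scenarios. The mean change and percentage change can err either way. The change is slightly too negative if loss follows low earlier PCS (about 0.1 to 0.2 points in the eight-visit simulation). It is too favourable by about 0.45 to 1.35 points if loss follows decline with ρ of 0.1 to 0.3. The upper end is nearly the whole planned precision of 1.4.

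All these sizes rest on assumed correlations, means and SDs. The documents give no difference between completers and non-completers, so neither the sign nor the size of the actual bias is known. They do not support saying that the bias is certain, that it is upward for change, or that a decline will be hidden.

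**What to change.** 1. Keep the observed-case tables as descriptive output. Beside each visit mean, show the baseline mean PCS of the same patients, so that a change in who responds is not read as a change in HRQoL.
2. Add a likelihood-based mixed model for repeated measures on all observed PCS visits, with visit, baseline CKD stage, stage-by-visit and baseline covariates. Report the Month-18 change with a 95% CI per stage and overall. This is compatible with the no-imputation rule.
3. Tabulate baseline characteristics, including PCS and CKD stage, for completers and non-completers.
4. Add a delta-adjusted sensitivity analysis in which unobserved Month-18 scores are, for example, 1 to 5 points worse. With 40% missing this moves the mean by 0.4 × 1 = 0.4 to 0.4 × 5 = 2.0 points, a range that spans the 1.4-point precision.

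The cost is analysis-plan wording and modest programming; no new data are needed. The mixed model replaces an unstated missing-completely-at-random assumption with missing at random. It removes only part of the bias if loss depends on unseen change, which is why the delta analysis is needed as well.
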